### Sample size

This is a pilot study and a formal sample size is not computed. We anticipate that a total of 20 participants will be recruited to the pilot study within two months.

### Data management and confidentiality

The applications used in this study including Zoom Healthcare provided by MS Ireland which uses password protected calls with random meeting ID’s and locked rooms after entry. It is accredited as a tele-health communication system. Also, Qualtrics Survey Software (account held by School of Allied Health, Univeristy of Limerick) are accepted to be used for research as a secured and confidential by the University of Limerick. Data will be handled confidentially and will be stored in accordance with Data Protection Policy at the University of Limerick and in line with the Health Research Regulations 2018 and General Data Protection Regulation (GDPR). All participants will be anonymised by given a unique identifying number and will be entered in a password-protected laptop. Data collected will be accessed only by the team of the study including; HD, KR, SC, RG and DM. All data collected during the study will be entered securely and confidentially in the same laptop by HD. The data will be stored for seven years then all electronic files will be deleted permanently. The full protocol and supplementary Materials are available in an open repository. There are no plans to make the participant dataset open access.

### Statistical methods

SPSS software (Version 26.0. Armonk, NY: IBM Corp) will be used for statistical analysis:

•
*The primary outcomes* will be analysed using descriptive statistics (numbers, means, and percentage) with 95% confidence interval (CI). Medians and interquartile ranges will be reported where data are not normally distributed.

•
*The secondary outcomes* for the scores of ICIQ-OAB and King’s Health questionnaire at the baseline, and at the end of week 6 will be reported as mean scores with SD and changes in scores between baseline, and week 6 will be examined using T-tests to provide a quantitative indicator of the significance of the changes in the assessment measures following stimulation sessions. The non-parametric equivalent tests will be employed where data are non-parametric.

The incidence of nocturia, incontinence and urinary frequency and urgency will be reported across the two groups and differences will be quantified using a Chi-squared test.

The scale of Patient Perception of Intensity of Urgency Scale (PPIUS) will be assessed using descriptive statistics means and standard deviation (SD).

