### Specific objectives

The overreaching aim of this study is to assess whether transcutaneous tibial nerve stimulation (TTNS) is feasible as a treatment for bladder storage symptoms in people with MS. In particular, the study will explore the feasibility and acceptability of TTNS application in people with MS by addressing the following specific objectives:

*The primary objectives are* to a) assess the recruitment and retention rates, b) investigate the completion rate and appropriateness of outcome measures by participants; c) assess safety by reporting the number of participants with adverse events; d) determine participants’ adherence to the treatment protocol, and e) assess participant’s satisfaction with TTNS application.

*The secondary objectives are to* a) evaluate the preliminary effectiveness of TTNS in managing bladder storage symptoms in MS; and to b) determine the effect of TTNS on quality of life in people with MS.

Addressing these objectives will establish a foundation for future definitive randomised trial to explore the efficacy of TTNS on bladder storage symptoms in MS.

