### Study design

A single-arm experimental study to assess the feasibility of TTNS in MS bladder storage symptoms.

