### Outcomes

**Primary outcome measures**. A) Feasibility will be assessed by the proportion of participants who: are recruited to the study, complete assigned outcome measures, complete the 6-week intervention, and are lost to follow up. Also, feasibility will be assessed by the overall level of adherence achieved over the study period of 6-weeks through the self-report diary (
Anghel *et al*., 2019). Adverse events will be measured using a self-report diary and will include (but will not be limited to) any device related skin redness at the site of stimulation, discomfort at the stimulation site that might persist post treatment session. B) Acceptability (satisfaction) of TTNS application will be assessed using a self-report questionnaire developed by the researchers containing 5-point Likert scales: 1= “strongly disagree”; 2= “disagree”; 3= “neutral”; 4= “agree”; 5= “strongly agree”.

**Secondary outcome measures** include the followings:

The storage symptoms will be assessed by ICIQ-OAB (
Abrams *et al*., 2018;
Zappavigna & Carr, 2015). It has grade A for validity, reliability and responsiveness to change established with rigour on one data set. The total score ranges from 0 to 16 with higher values indicating increased symptom severity. Bother scales are not incorporated in the overall score (
Abrams *et al*., 2006).Severity of frequency, nocturia, and incontinence will be assessed by using a standard 3-day bladder diary (
Jimenez-Cidre *et al*., 2015;
Nambiar & Lucas, 2014). Number of episodes of frequency, nocturia, and incontinence/ 72 hours will be calculated and compared from baseline with higher values indicating increased symptom severity.Severity and intensity of urgency will be assessed using Patient Perception of Intensity of Urgency Scale (PPIUS) (
Notte *et al*., 2012). Number of urgency episodes and severity of urgency/72 hours will be calculated and compared from baseline. The total score ranges from 0 to 4 with higher values indicating increased symptom severity.Quality of Life (QoL) will be evaluated by using King’s Health Questionnaire (
Nambiar & Lucas, 2014;
Okamura *et al*., 2009;
Pat Ray *et al*., 2003). A change from baseline of 5 points or higher on most of the King’s Health Questionnaire domains represents a clinically meaningful improvement in health-related quality of life after treatment (
Kelleher *et al*., 2004).

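### The secondary objectives and t-tests invite an effect conclusion that a single arm of about 20 people cannot give; report paired change with a 95% CI instead

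*Protocol article*

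**What the plan says.** Study design describes "A single-arm experimental study to assess the feasibility of TTNS in MS bladder storage symptoms". Under Sample size the authors write "This is a pilot study and a formal sample size is not computed", followed by "We anticipate that a total of 20 participants will be recruited to the pilot study within two months".

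The two secondary objectives under Specific objectives are worded differently. The first is to "evaluate the preliminary effectiveness of TTNS in managing bladder storage symptoms in MS". The second is to "determine the effect of TTNS on quality of life in people with MS".

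Statistical methods divides the reporting as follows:
- The primary feasibility outcomes get descriptive statistics with 95% confidence intervals.
- ICIQ-OAB and KHQ get a mean and SD at baseline and at week 6. Change is then examined by t-tests, or non-parametric equivalents, "to provide a quantitative indicator of the significance of the changes in the assessment measures following stimulation sessions".
- Nocturia, incontinence, frequency and urgency are compared between two groups by a chi-squared test.

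Outcomes cites a benchmark for quality of life: "A change from baseline of 5 points or higher on most of the" KHQ domains is described as a clinically meaningful improvement. Statistical methods does not refer to it.

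**The concern.** The quality-of-life objective is causal, and the chosen tool is a test of change within one arm. Nothing in the design separates an effect of TTNS from other reasons for scores to fall. The protocol's own procedures supply several such reasons. People with at least one storage symptom come forward themselves. They apply the treatment knowing what it is, complete every outcome by self-report, and are called each week by a member of the research team.

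At stake is how the result will be read. Followed as written, the plan yields a statement that quality of life or symptoms changed significantly after TTNS, under an objective that calls this the effect of TTNS. The quantity that would help a later randomised trial is the size of the change and its uncertainty. The article does not plan to report an interval for it.

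**Working it through.** **Inputs.** n = 20 (Sample size). One arm (Study design). The same people are measured at week 0 and week 6 (Participant identification and consent), so the t-test is read as paired. The article states no alpha, power or target difference, so there is no figure of the plan's own to reproduce. Two-sided alpha of 0.05 is assumed.

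**1. What the test addresses.** In one arm:

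expected change = TTNS effect + non-specific change

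The paired t-test takes the whole sum to be zero as its null hypothesis. No comparator allows the two terms to be estimated separately.

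**2. How often it is significant when TTNS does nothing.** Let δ be the non-specific change divided by the SD of change. The test statistic is then noncentral t with 19 df and noncentrality δ√20. The critical value is t(0.975, 19) = 2.093, and the opposite tail is negligible.

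| δ (assumed) | δ√20 | P(p < 0.05) with zero TTNS effect |
|---|---|---|
| 0.3 | 1.34 | 25% |
| 0.5 | 2.24 | 56% |

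The values of δ are illustrations; the documents give none.

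**3. What a non-significant result would mean.** By the same formula, 80% power at n = 20 needs a mean change of 0.66 SD of change. Power at 0.2 SD is 13%. A p-value above 0.05 is therefore little guide either.

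**4. Precision of the estimate.** The 95% CI half-width is t(0.975, n−1)/√n in units of the SD of change:
- n = 20: 2.093/4.472 = 0.47
- n = 16 completers (assumed): 2.131/4 = 0.53

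For a KHQ domain at n = 20, with the SD of change assumed because the article gives none:

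| SD of change (points) | Half-width (points) |
|---|---|
| 10 | 4.7 |
| 15 | 7.0 |
| 20 | 9.4 |
| 25 | 11.7 |

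From an SD of change of 15 upwards, the interval extends further on each side than the 5 points cited under Outcomes. A p-value does not show this.

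**5. Why the visit SDs are not enough by themselves.** With equal SDs at both visits, SD of change = SD × √(2(1−r)). For r = 0.3, 0.5, 0.7 and 0.9 the multiplier is 1.18, 1.00, 0.77 and 0.45. The planned mean and SD at each visit leave the SD of change open unless r or the test statistic is also given.

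**6. Diary symptoms.** Outcomes plans to count episodes over 72 hours and compare them with baseline, which is a paired comparison of counts. Statistical methods instead names a chi-squared test between two groups. The study has one arm measured twice, so there are no two independent groups to compare, and that test does not fit.

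**The case against.** The strongest reply is that these are secondary aims of a feasibility study. The symptom objective claims only preliminary effectiveness, the background says randomised trials are required, and the article leaves efficacy to a later trial: "Addressing these objectives will establish a foundation for future definitive randomised trial to explore the efficacy of TTNS". This stands in part. The causal wording is confined to quality of life, and the article makes no confirmatory claim. It does not remove the mismatch between that objective and the design.

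A second reply is that the SD of change and its interval are table detail, normally left to an analysis plan, and can be recovered. With complete pairs and a reported paired t, SD of change = mean change × √n / t, and r = (s1² + s2² − SD of change²)/(2·s1·s2). That is correct. A reader might infer that these numbers will be unavailable to the definitive trial, but the article does not support that. Recovery fails only if a non-parametric test is used, pairs are incomplete, or neither t nor an exact p-value is reported. What remains is that the article allocates intervals to the primary outcomes and significance tests to the secondary ones. This is a stated choice, not silence.

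Third, p-values need not be banned. Labelling them exploratory would also do, and the fix allows it.

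**Conclusion.** The point holds as one of inference and reporting. A single-arm change in about 20 people cannot determine the effect of TTNS, and a significance test is a poor main summary of it. If non-specific change alone were 0.3 or 0.5 SD of change, the test would be significant about 25% or 56% of the time. The interval to be expected is ±0.47 SD of change with 20 complete pairs. The percentages rest on the assumed non-specific change and on two-sided alpha of 0.05. The half-width rests only on n = 20 and approximate normality of the changes.

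Four stronger readings are tempting but unsupported:
- **A 5-point worsening would meet the KHQ threshold.** The sentence under Outcomes goes on to call the change an improvement, so it would not.
- **A non-significant result could stop a useful treatment.** No decision in the article depends on a secondary p-value.
- **Regression to the mean has a known size here.** Entry needs only one storage symptom, with no severity cut-off, so the documents give no basis for a figure.
- **A family-wise error rate can be calculated.** The number of KHQ domains is not stated, the scores overlap, and the chi-squared tests on paired data cannot be taken as valid 5% tests.

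The feasibility objectives are unaffected.

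**What to change.** 1. Reword both secondary objectives, for example: *to describe the change from baseline to week 6 in storage symptoms and in quality of life; no inference on efficacy will be drawn*.
2. In Statistical methods, make the main secondary result the mean (or median) paired change with its 95% CI and the SD of change. Do this for ICIQ-OAB, each KHQ domain and the diary counts. Adding the week 0 to week 6 correlation would spare readers the back-calculation.
3. For KHQ, state where each interval lies relative to the 5-point improvement cited under Outcomes.
4. Drop p-values or label them exploratory. Replace the chi-squared comparison of two groups with the paired summary of the diary counts.

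The cost is a change of wording. The same data are collected, and Study status says the study had yet to commence. The one downside is less prominence for p-values.

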### Dissemination

The findings of the study will be shared with MS Ireland to be distributed to people with MS and healthcare professionals (HCPs). Also, the study will be submitted for publication to a peer reviewed journal.

### Study status

The study is yet to commence. It is due to commence in September 2020

## Conclusion

To the authors’ knowledge, no feasibility studies have been conducted to evaluate the feasibility of TTNS application for managing storage bladder symptoms in MS. It is anticipated that assessing the feasibility for the application of TTNS among people with MS will contribute to proceed with a definitive randomised trial.

## Data availability

### Underlying data

No underlying data is associated with this article.

### Extended data

Open Science Framework: Transcutaneous tibial nerve stimulation for the treatment of bladder storage symptoms in people with multiple sclerosis: Protocol of a single-arm feasibility study.

https://doi.org/10.17605/OSF.IO/Q2N9E (
[name], 2020)

This project contains the following extended data:

-Appendices.docx (recruitment letter, screening form, demographic data sheet, 3- day bladder diary, adverse events report diary, adherence to treatment protocol and the questionnaire for acceptability of treatment)

### Reporting guidelines

Open Science Framework: SPIRIT checklist for ‘Transcutaneous tibial nerve stimulation for the treatment of bladder storage symptoms in people with multiple sclerosis: Protocol of a single-arm feasibility study’
https://doi.org/10.17605/OSF.IO/Q2N9E (
[name], 2020)

Data are available under the terms of the
Creative Commons Zero “No rights reserved” data waiver (CC0 1.0 Public domain dedication).
